### Outcomes

The primary outcome of the study will be 48-month change in MMSE scores. Secondary outcome will be 48-month change in neuropsychological test scores, including FAB, RAVLT, PMT, Stroop Color Word Interference Test, Attentive Matrices, Raven’s Progressive Matrices, TMT, Copying of Drawings with and without landmarks, and in GDS, SF-36, MAC-Q, PASE and AAHPERD fitness scores. Another outcome measure will be a composite cognitive score, which will be calculated for assessing the overall changes in cognitive performance. Each cognitive score will be standardized into a z score, by subtracting the baseline mean and dividing by the baseline standard deviation of the group. Regarding tests with more than 1 part, the standardization will be performed for each individual part. All z scores will be then averaged to calculate the composite cognitive score at each of the five time points (baseline, and 12, 24, 36 and 48 months). A positive score will point out a gain in cognitive performance, while a negative score a loss.

### Sample size calculation

Sample size calculations were based on the findings of previous studies and were performed separately for each category group. For heathy group, considering that MMSE scores decline 0.3 points in 4 years, we considered 0.6 points the minimal clinically important difference and used a Standard Deviation (SD) of 1.2 [38]. For SMC group, since that annual decline in MMSE score vary between 0.46 and 1.32 and that SD may vary between 1.48 and 2.6 [39], we considered 1.3 points the minimal clinically important difference and used a SD of 2.6. For MCI group, considering that the annual decline in MMSE score vary between 0.1 and 1.1 [40] and that SD may vary between 0.3 and 3.2 [41], we considered 1.6 points the minimal clinically important difference and used a SD of 3.2. Considering the percentage of drop-outs in previous similar studies and the length of the present study, we assumed a 30% attrition rate. Using an α level of less than 0.05, 90 participants per arm group will guarantee a power of 0.80.

### Blinding

The staff involved in collection of outcome measures and the data analysis is blinded to randomization assignment. During each follow-up evaluation, participants and examiners cannot provide or request information about the exercise program that subjects are performing.

### Randomization

After the baseline assessment, the participants of each category groups A, B and C were randomly assigned to one of the two groups (CG and EG) by using 1:1 blind randomization. For the randomization, a scheme generated via a computerized random number generator was used.

### Statistical analysis

Data will be analysed using the SPSS statistical software package (IBM, v.20.0, Chicago, IL, USA). Variables will be examined for outliers and extreme values by means of box and normal quantile-quantile plots, Shapiro-Wilk’s and Kolmogorov-Smirnov’s tests. When normal distribution cannot be accepted, the transformed variable (square, square root, logarithmic, reciprocal of square root or reciprocal transformations) will be reviewed. For normally distributed continuous variables, arithmetic means and SDs will be calculated, while for not normally distributed continuous variables, median, 25th and 75th percentiles will be calculated, according to the shaped distributions of two groups, as assessed by visual inspection of population pyramids. Sampling homogeneity (or baseline differences between groups) will be examined by means of chi-square (χ^2^) for categorical variables, independent-samples t-test for normally distributed variables and Mann-Whitney U test for not normally distributed variables. Differences between groups (experimental group vs. control group) and changes in the cognitive performance during the trial will be evaluated by means of Repeated Measures Analysis of Covariance (RM-ANCOVA) in the intention to-treat and complete-case analyzes, or with Linear Mixed Model analysis (LMM). The evaluations in the different time-points will be considered as the within-subjects factor whereas the two groups will be considered as between factor. Age, education level and gender will be included as covariates. The assumptions of equality of variances and sphericity will be assessed by means of Levene’s test and Mauchly’s test, respectively. The Greenhouse-Geisser or the Huynh-Feldt correction will be applied if the assumption of sphericity will be violated. Post-hoc independent-samples t-test will be performed to detect significant differences among trial conditions.

A *p*-value < 0.05 will be considered statistically significant.

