**Methods/design:**

EPD is a parallel group, double-blind, randomized controlled trial. Community-dwelling volunteers aged 50 years or more are being recruited from different community centers and screened for eligibility. Enrolled subjects are being divided in 3 groups: a) without subjective or objective cognitive impairment, b) with subjective memory complaints, and c) with mild cognitive impairments. Participants in each group (at least 180) are being randomly assigned (1:1) to an experimental group, performing a supervised training including aerobic and resistance exercises of moderate/high intensity, or to a control group. Primary outcome will be 48-months changes in Mini Mental State Examinations. Secondary outcomes will be changes in several cognitive tests including a composite cognitive score. Time points will be at baseline, and at 6, 12, 24, 36 and 48 months. Statistical analysis will be done as intention to treat, complete case and mixed model analysis.

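### The intention-to-treat analysis is assigned to repeated-measures ANCOVA, which drops anyone with a missed visit, and the mixed model that could keep them is only an unranked alternative

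*Protocol article*

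**What the plan says.** The primary endpoint is clear: "The primary outcome of the study will be 48-month change in MMSE scores" (Outcomes). The schedule has six assessments: "Time points will be at baseline, and at 6, 12, 24, 36 and 48 months" (abstract, Methods/design). The composite score is described at one fewer, "at each of the five time points (baseline, and 12, 24, 36 and 48 months" (Outcomes), so month 6 drops out there.

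The Statistical analysis section gives the method as "Repeated Measures Analysis of Covariance (RM-ANCOVA) in the intention to-treat and complete-case analyzes, or with Linear Mixed Model analysis (LMM". Two further sentences show that the ANCOVA is the classical repeated-measures form: "The evaluations in the different time-points will be considered as the within-subjects factor" and "The Greenhouse-Geisser or the Huynh-Feldt correction will be applied if the assumption of sphericity will be violated". Age, education and gender are the covariates, and SPSS is the software.

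The abstract puts the same plan differently: "Statistical analysis will be done as intention to treat, complete case and mixed model analysis". On missing data, the only statement is in the sample size section: "we assumed a 30% attrition rate". Separately, the Control group section says that controls who raise their activity from light to moderate or vigorous intensity are excluded from the group.

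**The concern.** Classical repeated-measures ANCOVA needs a complete row of data for each participant. One missed visit removes the person altogether. Assigning that method to the intention-to-treat analysis, in a four-year trial that expects to lose 30% of its participants, sets the method against the label.

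The linear mixed model is the one named method that keeps participants with partial follow-up. It is joined by *or* in the Methods and by *and* in the abstract, with no rule for when it applies and no order among the three routes. The analysis that yields the headline MMSE result is therefore not fixed in advance.

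Two things are at stake: whether the result reported as intention-to-treat describes the randomised groups or only the completers, and whether the choice among routes could be made once results are known. The arms ask very different things of participants (three supervised classes a week for 48 months, against usual lifestyle), so drop-out that differs by arm is plausible, though the article gives no data on it.

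**Working it through.** **1. The plan's own sample size.** The inputs are the differences and SDs in Sample size calculation: 0.6/1.2, 1.3/2.6 and 1.6/3.2. Each gives a standardised difference d = 0.5. With alpha 0.05 (two-sided, which is not stated but reproduces the figure) and power 0.80:

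- n = 2 × (1.960 + 0.842)² / 0.5² = 62.8, so 63 evaluable per arm
- 63 / (1 − 0.30) = 90 per arm, which matches the article

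The two-sample t-test has power 0.795 at 63 per arm. The sample size therefore already counts on about 63 completers.

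**2. Who the intention-to-treat run would include.** With 30% lost by month 48, at most 0.70 × 90 = 63 per arm have complete data, which is 126 of 180 per category group. At least 27 randomised participants per arm are left out. Without imputation, the complete-case run contains the same people.

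**3. Missed interim visits.** There are four visits between baseline and month 48 (6, 12, 24 and 36 months). The article gives no miss rate for them, so q is assumed, independent across visits and additional to the 30%. Complete cases per arm = 63 × (1 − q)⁴. Power is for the unadjusted t-test at d = 0.5, with n rounded.

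| q per interim visit | complete cases per arm | power |
|---|---|---|
| 0% | 63 | 0.80 |
| 2% | 58 | 0.76 |
| 5% | 51 | 0.71 |
| 10% | 41 | 0.61 |

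**4. Does the choice of route matter?** Two illustrative simulations were run; all drop-out settings are assumed.

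*No true effect:* 90 per arm, about 30% drop-out, SD of 48-month change about 1.07, and drop-out depending on decline already observed.

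| how drop-out depends on decline | bias, listwise | bias, likelihood on all visits |
|---|---|---|
| same way in both arms | 0.005 | 0.003 |
| exercise arm only | 0.13 | −0.01 |
| opposite directions in the two arms | 0.28 | 0.00 |

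In SD units the last two listwise biases are 0.13/1.07 = 0.12 and 0.28/1.07 = 0.26, against a design effect of 0.5.

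*SMC setting:* true difference 1.30, SD of change 2.6, 30% drop-out per arm, drop-out driven by observed decline in one arm only, logit slope 0.5 to 1, and baseline-to-48-month correlation 0.5 to 0.7. Listwise estimates ran from 0.90 to 1.68. They fell on either side of the truth according to which arm's drop-out followed decline. The likelihood analysis gave 1.29 to 1.31. When both arms shared the same dependence, listwise gave 1.28 to 1.30.

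**The case against.** The strongest reply is that naming intention-to-treat and complete-case as two separate ANCOVA runs only makes sense if missing values are to be filled in for the first. Repeated-measures ANCOVA on suitably imputed data for everyone randomised is a legitimate intention-to-treat analysis, and a condensed article may leave the imputation method to the analysis plan. This stands in part. A reader might infer that the method can never be intention-to-treat, or that the two runs are certainly identical; the article supports neither, because it does not rule imputation out. A reader might also assume that last values would be carried forward, but the article never mentions that. What imputation would not settle is which analysis is primary, or whether the mixed model is an alternative or an addition.

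The bias figures depend on drop-out that differs by arm. They also assume that missingness depends on observed values, which is the condition under which a likelihood analysis does well by design. Both qualifications are right: with equal dependence the methods agree.

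Two features limit selective reporting without removing it. On the abstract's wording all three analyses will be done, and the staff who analyse the data are blinded to assignment. Blinding hinders choice by direction of effect, but not choice by p-value.

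**Conclusion.** The point holds as an inconsistency in what the article fixes. It gives the intention-to-treat analysis a method that cannot hold participants with missed visits unless an unstated imputation is used, while expecting to lose 27 of 90 per arm. It names no primary analysis of 48-month MMSE change, and the abstract and the Methods disagree on the role of the mixed model.

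The main harm is possible bias and an open choice. Under the assumed arm-specific drop-out, the listwise bias was about 0.12 to 0.26 SD with no true effect, and its sign depended on which arm's drop-out followed decline. That range is illustrative and shrinks to about zero if drop-out relates to decline equally in both arms.

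Two stronger conclusions are tempting but not supported. The planned power is not lost through attrition as such, since 63/0.70 = 90 already pays for it; the fall to between 0.76 and 0.61 needs the assumed 2% to 10% misses at each interim visit. Nor does the article make a complete-case analysis primary, because it ranks nothing. The requirement of six complete visits applies to MMSE; the composite score is described at five.

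This should be fixed, but it does not invalidate the design.

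**What to change.** In Statistical analysis, name one primary analysis of 48-month MMSE change: a linear mixed model with visit, arm and arm-by-visit terms and the planned covariates (age, education, gender), fitted to all randomised participants in their randomised arm with every available visit. The result to report is the arm contrast at month 48.

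Keep repeated-measures ANCOVA as a complete-case sensitivity analysis, and replace the *or* by this order. Bring the abstract sentence into line.

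Reconcile the exclusion of controls who change activity intensity with the intention-to-treat set by saying whether their data stay in the primary analysis. The Control group section leaves this open.

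The mixed model has a cost of its own: it relies on data being missing at random. A sensitivity analysis for drop-out that depends on unobserved decline should therefore accompany it.

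The change is to wording. It needs no new data and no larger sample, and the mixed model is already among the methods the article plans to run in SPSS. The extra work is the added sensitivity analysis.

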### Baseline and successive assessments

The potential eligible participants are invited at the Center for Research and Training in Medicine of Aging of the University of Molise to an in-person assessment that includes: 1) general conditions and health status, 2) neurocognitive performances, and 3) physical fitness levels. The three assessments are performed individually in 3 non-consecutive days. The baseline assessments were also used to screen the participants to exclude those that meet exclusion criteria, and to categorize them in A, B or C category groups. Successively, the assessment sessions are repeated at 6, 12, 24, 36 and 48 months to evaluate the differences among time-points.

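### The primary outcome is 48-month MMSE change, but the planned repeated-measures model names no 48-month contrast and does not list baseline MMSE as a covariate

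*Protocol article*

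**What the plan says.** The Outcomes section is unambiguous: "The primary outcome of the study will be 48-month change in MMSE scores". The Sample size calculation works separately in the three category groups and concludes: "Using an α level of less than 0.05, 90 participants per arm group will guarantee a power of 0.80".

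Under Baseline and successive assessments, "the assessment sessions are repeated at 6, 12, 24, 36 and 48 months to evaluate the differences among time-points". With baseline, that makes six time points.

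The Statistical analysis section compares the arms by "RM-ANCOVA) in the intention to-treat and complete-case analyzes, or with Linear Mixed Model analysis (LMM"). The structure is: "The evaluations in the different time-points will be considered as the within-subjects factor whereas the two groups will be considered as between factor". On adjustment it says "Age, education level and gender will be included as covariates". Sphericity checks and corrections follow, then "Post-hoc independent-samples t-test will be performed to detect significant differences among trial conditions", with a threshold of p-"value < 0.05 will be considered statistically significant". The section does not say which term (group, group-by-time or a month-48 contrast) answers the primary question.

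**The concern.** The outcome and the sample size concern one quantity, the difference between arms in change from baseline to month 48. The analysis section describes a model that yields several tests and ties none of them to that quantity. The Mauchly, Greenhouse-Geisser and Huynh-Feldt steps matter only for within-subject tests with more than one degree of freedom, so the text points towards an overall group-by-time test, which has 5 degrees of freedom with six time points.

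Two things are at stake.

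- **Interpretation.** An overall interaction can be significant because of a difference at any visit, including one that has gone by month 48. The Discussion gives as a purpose of the trial to learn whether benefit outlasts the first 6 to 12 months, and this test alone cannot answer that.
- **Efficiency.** Baseline MMSE is measured on everyone and would be expected to predict later MMSE, yet it is missing from a covariate list that is otherwise specific.

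**Working it through.** **Inputs from the article.** Difference and SD: 0.6 and 1.2 (no impairment), 1.3 and 2.6 (SMC), 1.6 and 3.2 (MCI). The ratio is 0.5 in each group. Alpha 0.05, power 0.80, attrition 30%, allocation 1:1.

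**Assumptions.** The article does not give the correlation ρ between baseline and 48-month MMSE; 0.3 to 0.9 is used in the formulas, and 0.5 and 0.7 in simulation. It does not say whether the SDs are of change or of scores; they are taken as SDs of change unless noted. The test is taken as two-sided, which reproduces the stated N. MMSE variance is taken as equal over time.

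**1. The stated N.** n = 2(1.96 + 0.842)² / 0.5² = 62.8, so 63 per arm; 63 / 0.70 = 90. This matches exactly. Power at 63 per arm is 0.80. The calculation therefore describes one comparison of two means.

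**2. Adjusting the 48-month comparison for baseline.** With score variance σ², change has variance 2(1 − ρ)σ², and the 48-month score given baseline has (1 − ρ²)σ². The ratio is (1 + ρ)/2. Power is Φ(0.5 / √(2 × ratio / 63) − 1.96).

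| ρ | Variance ratio | Power at 63 per arm | Per arm for 80% power, after 30% dropout |
|---|---|---|---|
| 0.3 | 0.65 | 0.94 | 59 |
| 0.5 | 0.75 | 0.90 | 69 |
| 0.7 | 0.85 | 0.86 | 78 |
| 0.9 | 0.95 | 0.82 | 86 |
| unadjusted | 1 | 0.80 | 90 |

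If the SDs are instead SDs of scores, power moves from 0.66 to 0.84 at ρ = 0.3, from 0.80 to 0.90 at 0.5, and from 0.95 to 0.98 at 0.7. The gain keeps its direction.

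**3. Power of the planned tests.** Simulation with 63 per arm, six visits, ρ of 0.5 or 0.7, constant or decaying correlation, 3,000 runs per scenario, Greenhouse-Geisser correction, and no age, education or gender effects. The 48-month effect is 0.5 SD of change. "Early" means half the effect at month 6 and all of it from month 12.

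| Test | Linear growth to month 48 | Early and sustained |
|---|---|---|
| Group-by-time | 0.74–0.76 | 0.83–0.91 |
| Group main effect | 0.18–0.38 | 0.40–0.78 |
| 48-month change, unadjusted | 0.79–0.80 | 0.79–0.81 |
| 48-month, baseline-adjusted | 0.85–0.90 | 0.84–0.90 |

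A t-test on raw 48-month scores has power of about 0.80 at ρ = 0.5 and 0.57–0.58 at ρ = 0.7.

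**4. A transient effect.** Same set-up with 2,000 runs: 0.5 SD of change at months 6 and 12, two thirds of that at 24, one third at 36, nothing at 48. The group-by-time test is significant in 89–99% of runs. The 48-month change test stays at about 5%.

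**5. The post-hoc t-tests.** With no true effect, the repeated-measures tests hold about 5%. If five follow-up visits were each tested at 0.05 without an overall test first, at least one would be significant in 11–18% of runs at ρ of 0.5 or 0.7. Over visit correlations of 0.3 to 0.7 a second simulation gives 15–21%. If the t-tests followed only a significant interaction, the rate would be 1.3–2.5%.

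**The case against.** A reader might infer that the plan wastes power and inflates the error rate. The documents do not support that as a general statement.

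- **Method.** RM-ANCOVA is not the only one named. A linear mixed model is offered as well, and the remedy is a specification of that model.
- **Baseline is not ignored.** As a level of the time factor it contributes to the group-by-time test, and because the outcome is change, that interaction is the natural reading. Nothing makes the group main effect primary, so its low power should not be held against the plan.
- **Power.** Against an unadjusted change test the interaction loses about 4 to 5 points under linear growth, and it gains if the effect is early and sustained. The 80% claim never relied on baseline adjustment.
- **Error.** The article says the t-tests compare trial conditions. It does not say that they are run at every visit, or that one could replace the 48-month result. Post-hoc tests ordinarily follow a significant overall test, and then the rate under no effect is below 5%.
- **Condensed article.** An analysis plan that is not shown may name the contrast and the handling of multiple tests.

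All of this stands against the stronger reading. It does not remove the narrower point. The article commits to a model and a specific covariate list, and neither is tied to its primary outcome. The interaction's extra power for early effects comes from testing a different hypothesis, as the transient case shows. Offering a mixed model with the same factors and covariates does not settle which contrast is primary.

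**Conclusion.** The point holds as a mismatch between endpoint and analysis and as efficiency given up; it does not make the analysis invalid. Within the Statistical analysis section, no named test isolates the quantity on which the trial was sized. Adding baseline MMSE to a month-48 comparison would be worth about 2 to 14 percentage points of power over ρ from 0.9 to 0.3, starting from 0.80. That range rests on the assumed correlation and on reading the stated SDs as SDs of change.

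The t-tests are a lesser matter. They drop the three covariates and carry no stated adjustment. A false-positive rate of roughly 11–21% would arise only if they were run ungated at five visits and read as confirmatory, which the text does not state. The change is worth making, because the gain is free and it settles which result answers the 48-month question.

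**What to change.** In the analysis plan, for each category group:

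- Use the linear mixed model already named, with MMSE at months 6, 12, 24, 36 and 48 as outcomes. Take arm, visit, arm-by-visit, baseline MMSE, baseline-by-visit, age, education and gender as fixed effects. Baseline then leaves the repeated outcomes; a constrained mixed model that keeps it there is an acceptable alternative.
- Name the arm difference at month 48 from that model as the single primary test at 0.05.
- Replace the post-hoc t-tests by contrasts from the same model at the earlier visits, labelled supportive.
- Analyse each secondary score in the same way, with its own baseline as covariate.

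The cost is wording. MMSE is already part of the baseline assessment, so no new data are needed, and the sample size does not change. The choice should be fixed before the analysts are unblinded.

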## Discussion

We present the design of the ongoing EPD Study. To the best of our knowledge, this RCT represents the first long-duration study analyzing the effects of a structured, individualized and multi-modal exercise programs in older adults with different risk of dementia. The hypothesis is that engaging in a supervised program of exercise, consisting of aerobic/resistance training performed for 60 min, 3 times a week for 48 months could be efficacious in averting or at least slowing the memory decline in subjects with different risk of dementia, from normal (with low risk), to SMC (with moderate risk), up to MCI (with high risk) subjects.

Results from the EPD trial will be reported according to the CONSORT guidelines (http://www.consort-statement.org/) to exceed the limits related to the poor methodological quality of many previous RCT. We intend to complete data collection in May 2019 to carry out a study with a larger population sample and to verify if the positive effect of exercise continues beyond the first 6–12 months, that usually is the maximal duration of exercise interventions in the previous studies [42].

The main strengths of this study are its randomized prospective design, the utilization of community-dwelling elderly people, the long period of intervention, and the adequate sample size. Other important merits of this study are the high reproducibility and the home-based nature of the intervention.

Furthermore, the proposed exercise program involves multiple components of fitness including aerobic, strength, balance and flexibility training, and such multimodal approach is expected to give the best results on cognitive function, compared to aerobic exercise alone, as suggested by previous study and meta-analysis [43–46].

Concerning the mechanism by which exercise could influence cognition, the actual evidences do not allow definitive answers. Several potential mechanisms could contribute to improve brain health and cognitive performance as suggested by Kennedy et al. [47]: promotion of cardiovascular health, production of Brain Derived Neurotrophic Factor (BDNF), improvement of insulin sensitivity, reduction of stress and inflammation. All these potential pathways can have a role by which exercise may maintain or improve cognitive functioning, especially in the context of the aging brain. The review of Kennedy et al. [47] also stated that a greater understanding of these mechanisms is necessary to provide potential biomarkers for investigating the efficacy of differing exercise regimes on cognitive outcomes. In fact, the absence of univocal biomarkers or parameters to assess effects of exercise on brain health represents another important problem in this particular field of research that make difficult the comparability of the different studies outputs. Another problem is the variability of the results obtained in the different study of literature: Landrigan et al., [48] in a recent meta-analysis, investigated the effect of resistance exercise on cognition, and they concluded that resistance training appears to have positive effects on cognition, but future researches are needed to determine why the effects are so variable. Finally, no evidences exist concerning the “optimal dose of exercise” in order to have benefit on cognition, and studies are needed comparing the effects of trainings with different session duration and frequency as suggested by Sanders et al. [49].

However, despite these difficulties, different authors supported the hypothesis that exercise can have an important role in promoting brain health [50]. The first important role can be the prevention of dementia onset due to the amelioration of several cardiovascular risk factors, such as diabetes, hypertension, obesity and depressive symptoms, which are recognized as a reversible risk factor for dementia [51]. The second role of the exercise is a direct effect on brain health: in fact, exercise appears to have a beneficial effect in preserving neurogenesis [52, 53], and favoring neuroplasticity [54]. Furthermore, beneficial effects of exercise were demonstrated on secondary dementia such as dementia inducted by Chronic Obstructive Pulmonary Disease [55].

Nevertheless, despite the increasing interest on the exercise effects on brain health, some authors claimed that the protective effects of exercise on dementia or cognitive impairment may be overvalued [56, 57]. Also, previous studies showed overall that physical fitness levels are not strongly correlated with cognitive performance [58]. This discrepancy in author opinions and results suggests that further high-quality studies, and interventional studies including long follow-up periods and high reproducible exercise interventions, are necessary.

The EPD trial will: (a) evaluate the effectiveness of multimodal exercise program of 48 months in improving neurocognitive functions in individuals aged 50 years or older at different risk of AD; (b) identify the category of subjects and the cognitive function that gets the best benefits from such modality of exercise; c) examine the possible mechanisms by which exercise improve cognition.

In conclusion, this study, if successful, may represent an affordable and safe method to demonstrate that exercise represents a protective tool to delay the onset of dementia and the cognitive impairment in older adults at risk, such as subjects with SMC or MCI. Results of this study are expected to have important public health implications and a profound impact on future AD prevalence.

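### The trial promises to identify the cognitive function that benefits most from exercise, but its stated analysis never compares the exercise effect between functions

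*Protocol article*

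**What the plan says.** The closing part of the Discussion lists what the trial will do. Item (b) is to "identify the category of subjects and the cognitive function that gets the best benefits from such modality of exercise". It is worded as a deliverable, with no exploratory label. This point concerns the cognitive-function half of that item only.

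The Outcomes section makes 48-month change in MMSE the primary outcome. It continues: "Secondary outcome will be 48-month change in neuropsychological test scores, including FAB, RAVLT, PMT, Stroop Color Word Interference Test, Attentive Matrices, Raven’s Progressive Matrices", followed by TMT and Copying of Drawings. That is eight named cognitive tests. It is ten scores if TMT A and B (Neurocognitive assessment) and copying with and without landmarks are counted separately. A composite of averaged z scores is a further outcome.

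The Statistical analysis section specifies RM-ANCOVA or a linear mixed model. Time point is the within-subjects factor, arm is the between-subjects factor, and age, education and gender are covariates. Post-hoc t-tests compare trial conditions. Cognitive test or function is not a factor in any model. The decision rule is a single line: a p-"value < 0.05 will be considered statistically significant".

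**The concern.** Which function benefits most is a question about differences between effects. The described models answer another question, score by score: do the arms differ on this test? Significance on one test and not on another is weak evidence that the two effects differ, because each test has its own sampling error. The largest of several noisy estimates also tends to overstate its own true effect.

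At stake is a stated conclusion of the trial. With the analysis as described, a reader could be told that exercise acts specifically on one function when it helps all functions equally, or none. The MMSE conclusion is not affected.

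**Working it through.** **The plan's own figure first.** Sample size calculation states: "Using an α level of less than 0.05, 90 participants per arm group will guarantee a power of 0.80". The inputs are 0.6/1.2, 1.3/2.6 and 1.6/3.2, so d = 0.5 in every category.

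- n per arm = 2 × (1.960 + 0.842)² / 0.5² = 62.8, rounded up to 63.
- With 30% attrition: 63 / 0.70 = 90 per arm.

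The stated 90 is reproduced, taking alpha as two-sided. It is powered for MMSE only. Completers per arm are 90 × 0.70 = 63.

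**Assumptions the documents do not give.** Test statistics on the scores are equicorrelated, with correlation r from 0 to 0.7. The standard error of a standardised arm difference is √(2/63) = 0.178 SD. The effect sizes used below are illustrative.

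**Step 1: no effect on any score, one category.** With independent scores, the chance that at least one is significant in favour of exercise is 1 − 0.975^k. This gives 18.3% for k = 8 and 22.4% for k = 10. Counting either direction, it is 1 − 0.95^k, giving 33.7% and 40.1%. Simulation covers the correlated cases:

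| Scores | Direction | r = 0 | r = 0.3 | r = 0.5 | r = 0.7 |
|---|---|---|---|---|---|
| 8 | favouring exercise | 18% | 15% | 12% | 10% |
| 10 | favouring exercise | 22% | 18% | 14% | 11% |
| 8 | either direction | 34% | 30% | 25% | 19% |
| 10 | either direction | 40% | 35% | 29% | 21% |

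The rows favouring exercise are the relevant ones for a claim of benefit.

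**Step 2: the same true effect, 0.3 SD, on all 10 scores.** The expected z on each score is 0.3 / 0.178 = 1.68, so each score is significant in favour of exercise with probability P(Z > 1.96 − 1.68), about 0.39. With independent scores, the chance that some but not all are significant is 1 − 0.39^10 − 0.61^10, about 0.99. By simulation it is 91% at r = 0.3, 79% at r = 0.5 and 63% at r = 0.7. A mixed pattern is the usual result when no function is special.

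**Step 3: one function truly better, 0.5 SD against 0.3 SD elsewhere.** For 8 or 10 scores and r = 0.3 to 0.5, the better function has the largest estimate in only 46% to 58% of trials.

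**Step 4: what a proper comparison can deliver.** In the Step 3 scenario, a global arm-by-test interaction test at 0.05 has power of about 9% to 23% (8 or 10 scores, r = 0 to 0.7), and about 14% for 10 scores at r = 0.5. When it is significant in that last case, the largest estimate still belongs to the wrong function in about 29% of trials. A significant interaction alone therefore does not say which function is best.

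**The case against.** The strongest objection is that this is a condensed article and that the wording sits only in the Discussion. The aims in the Abstract and Background concern cognitive function or its decline overall. Rules for multiple secondary outcomes are commonly left to an analysis plan, which is not shown. The article does fix one primary outcome, labels the individual tests secondary, and plans a composite that summarises them.

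Much of this stands. A reader might infer that the plan is at fault for having no hierarchy or multiplicity adjustment across the secondary tests. The documents do not support that: unadjusted secondary outcomes under a single primary are a common trade-off, and such detail may stand elsewhere. A reader might also take the either-direction figures of 19% to 40% as the risk of falsely naming a function that benefits. They count results favouring control; the relevant range is 10% to 22%. Nor does the article say that a winner will be declared by significance. It gives no rule for choosing one.

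What the objection does not remove is the mismatch. The analysis section is detailed, down to transformations, sphericity corrections and post-hoc tests, yet no analysis in it addresses the promised comparison. Adjusting the separate p-values would not supply one.

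**Conclusion.** The point holds as a mismatch between a stated aim and the stated analysis. Score-by-score arm comparisons cannot support a conclusion that one cognitive function benefits more than another. With equal benefit of 0.3 SD on 10 scores and 63 completers per arm, the plan would show a mixed pattern of significance in about 79% of trials at r = 0.5 (63% to 99% for r from 0.7 to 0). With no benefit, at least one score would favour exercise at p < 0.05 in about 10% to 22% of trials per category.

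These sizes rest on assumed correlations, an assumed common effect and the planned attrition. The mismatch itself does not depend on them. The MMSE primary analysis and the 90 per arm are sound on this point.

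**What to change.** - In the Discussion, restate the cognitive-function part of aim (b) as exploratory.
- In Statistical analysis, report the 48-month arm effect on each cognitive test with a 95% CI. Use the baseline z scale already planned for the composite, with every score oriented so that higher is better.
- Fit one mixed model across tests with an arm-by-test interaction at 48 months.
- Make no claim that one function benefits more than another unless the interaction and the multiplicity-adjusted pairwise differences from the leading function both support it.

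The cost is a wording change and one extra model on data already being collected. The downside should be stated in the plan: the interaction test has only about 9% to 23% power if one function gains 0.5 SD and the rest 0.3 SD, and the pairwise condition lowers the chance further. A single best function will usually not be named. The primary outcome and sample size do not change, and no Holm procedure or hierarchy for the secondary tests is required.
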